### **3.5 Other Analysis Populations**

No other analysis populations are planned at this stage

## **4 General Issues for Statistical Analysis**

### **4.1 Analysis Software**

All analyses will be performed using a statistical package SAS/R/STATA.

### **4.2 Multiplicity, Multiple Comparisons and Interim Analyses**

There will be no multiplicity adjustment for this trial.

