### **1.3.4 Sample Size Determination**

There are currently no data on plasma glucagon levels from human trials using low-dose sulfonylureas in patients with type 1 diabetes. The sample size calculations are based on the data generated from the LEGEND-A trial [4] (NCT02830048 - completed) and interim analysis from the DEPTH trial (NCT03537131 – suspended due to the COVID-19 pandemic).

The LEGEND-A trial suggested glibenclamide (at a dose of 0.3mg/day) could change plasma glucagon levels in participants with type 2 diabetes by 30% (magnitude of effect), while the DEPTH trial suggested that participants with type 1 diabetes who experienced exercise-induced hypoglycaemia had mean plasma glucagon values of 5.54pmol/L (SD 2.14pmol/L) at the time of hypoglycaemia (defined as <3.3mmol/L).

For the non-diabetic control group, data from a clinical study in healthy volunteers [5], which used similar methodology and a plasma glucagon assay comparable to the one we will use in our trial, demonstrated that the mean plasma glucagon values during the hypoglycaemia plateau of 23.3 pmol/L (SD 5.7pmol/L).

These figures indicate that 20 participants with T1D, and 10 participants without diabetes (including 5% dropout) would give the LEGEND-D trial 80% power to detect a 30% increase in plasma glucagon levels (the primary endpoint) during induced hypoglycaemia (hyperinsulinaemic-hypoglycaemic clamp).

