#### 2.1.2 Primary Hypothesis under Investigation

The hypothesis to be tested for the primary analysis is given below:

$H_0$ : There is no difference in counter-regulatory plasma glucagon concentration (pmol/L) during induced hypoglycaemia compared to baseline (pre-treatment) in people randomised to glibenclamide at 0.3mg, 0.6mg or 3mg (**Table 3**) daily for 14-18 days.

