## **5 Statistical Methodology**

The statistical methodology for the main primary analysis is described below. Analyses will use the ITT population (section 3.2) for primary and exploratory endpoint(s), and safety population for safety endpoint(s). All statistical significance will be assessed using

an alpha value of 0.05 (95% confidence interval). The summary statistics and statistical estimates will be presented with one decimal place unless more decimal places are needed to interpret the data. All p-values will be rounded to 3 decimal places. All Tables and Figures documented in this SAP are shell versions of the anticipated results and output formats of the analyses to be conducted for the study.

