## 5.3 Primary Endpoint Analysis

### 5.3.1 Primary Efficacy Analysis

To determine whether people randomised to glibenclamide at 0.3mg, 0.6mg or 3mg daily for 14-18 days can change the counter-regulatory plasma glucagon concentration measured in pmol/L at 40min during induced hypoglycaemia compared to baseline (pre-treatment) in T1D group only. We will use 3 separate paired t-tests to compare plasma glucagon concentration (pmol/L) at baseline and at each glibenclamide dose step i.e. 0mg vs 0.3mg, 0mg vs 0.6mg, and 0mg vs 3mg. We will also use linear random effects model [6] using plasma glucagon concentration (pmol/L) at each glibenclamide dose step as dependent variable and including treatment, period, and sequence of treatment to account for within-subject correlation to quantify the magnitude and direction of the change (increase/decrease). We will also adjust for age, gender, body weight, height, SBP, DBP and resting heart rate.

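### Three unadjusted primary t-tests give about a 13% chance of falsely rejecting a primary hypothesis set at 5%, and the stated 80% power cannot be derived from the figures cited for it.

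*SAP*

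**What the plan says.** Section 2.1.2 of the SAP states a single null hypothesis, no difference in glucagon during induced hypoglycaemia from baseline, "in people randomised to glibenclamide at 0.3mg, 0.6mg or 3mg". Section 5.3.1 sets the test: "We will use 3 separate paired t-tests to compare plasma glucagon concentration (pmol/L) at baseline and at each glibenclamide dose step", that is "0mg vs 0.3mg, 0mg vs 0.6mg, and 0mg vs 3mg", in the T1D group only. It then adds a covariate-adjusted linear random effects model to quantify the size and direction of the change. Section 5 sets alpha at 0.05 for all significance testing, with 95% confidence intervals. Section 4.2 reads "There will be no multiplicity adjustment for this trial".

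On sample size, section 1.3.4 cites a 30% effect from a study in type 2 diabetes. It also cites a study of exercise-induced hypoglycaemia in which T1D participants "had mean plasma glucagon values of 5.54pmol/L (SD 2.14pmol/L) at the time of hypoglycaemia", and a healthy-volunteer mean of 23.3 pmol/L (SD 5.7). It concludes that 20 T1D and 10 non-diabetic participants, allowing for 5% dropout, "would give the LEGEND-D trial 80% power to detect a 30% increase in plasma glucagon levels (the primary endpoint".

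**The concern.** There are two separate problems.

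**Error rate.** Because the hypothesis covers all three doses and the SAP does not say which result decides it, a significant result at any one dose rejects it. Three tests at 0.05 then give the primary hypothesis more than a 5% false-positive rate. A single p-value of 0.04 among three doses could be reported as a positive primary result at 5%.

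**Power.** The power of a paired t-test depends on the SD of the within-person change. The SAP gives only the spread between people at one time point, with no correlation, no named test and no sidedness. It also names the 10 controls in the sentence about power for the primary endpoint, although sections 2.1.1 and 5.3.1 restrict that endpoint and its test to the T1D group. A reader cannot tell what the 80% refers to.

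**Working it through.** **Inputs from the SAP.** Alpha 0.05, taken as two-sided because of the 95% interval (section 5). Three comparisons sharing one baseline (section 5.3.1). T1D mean 5.54 and SD 2.14 pmol/L, a 30% increase, 20 T1D participants and 5% dropout (section 1.3.4).

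**Assumed, because the SAP does not give it.** The correlation ρ between a person's baseline and on-treatment values, with equal SDs at each clamp.

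**False-positive rate when no dose has an effect**

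1. If the three tests were independent: 1 − 0.95³ = 14.3%.
2. They are not independent, because each difference subtracts the same baseline. With equal variances and equal correlations between clamps, any two differences correlate at 0.5 whatever ρ is.
3. Simulating the three paired t-tests with that structure (200,000 trials) gives 12.6% to 12.8% at n = 19 or 20, or about 13%.
4. If the correlation of the differences departs from 0.5, the rate runs from about 14% (correlation 0) through 12.6% (0.5) and 10.7% (0.75) to about 9% (0.9).
5. Counting only false increases, the direction named in the primary objective (section 1.1.1), the rate is about 6.4%. A single two-sided test at 0.05 gives 2.5%.
6. With Holm, the two-directional rate is about 4.5%.

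**The SAP's power figure**

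Effect: 0.30 × 5.54 = 1.662 pmol/L. Evaluable: 20 × 0.95 = 19. SD of the paired difference: SDd = 2.14 × √(2(1 − ρ)). The noncentrality is 1.662 × √19 / SDd on 18 degrees of freedom, with critical value 2.101 at 0.05 and 2.639 at 0.05/3.

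| ρ | SDd | Noncentrality | Power at 0.05 | Power at 0.05/3 |
|---|---|---|---|---|
| 0 | 3.03 | 2.39 | 62% | 43% |
| 0.35 | 2.44 | 2.97 | 80% | 63% |
| 0.5 | 2.14 | 3.39 | 89% | 76% |
| 0.7 | 1.66 | 4.37 | 98.5% | 95% |

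The stated 80% is reproduced only if SDd is about 2.45 (ρ = 0.35) at n = 19, or about 2.52 (ρ = 0.31) if dropout is ignored and n = 20. Neither value is quoted. Using 2.14 directly as the SD of the difference gives 89% at n = 19 and 91% at n = 20. Treating the comparison as unpaired, 20 against 20 on the same figures, gives 69%. The comparison with controls (23.3 against 5.54) has power above 99%, so it is not the source of the 80% either.

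**Per-dose power with Holm, n = 19 (simulation)**

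| ρ | Unadjusted | Holm, all three doses work | Holm, only one dose works |
|---|---|---|---|
| 0 | 62% | 50% (−12) | 43% (−19) |
| 0.35 | 80% | 72% (−8) | 63% (−17) |
| 0.5 | 89% | 85% (−5, before rounding) | 76% (−13) |

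**The case against.** The best defence is that section 1.2 calls the trial a pilot, all three comparisons are pre-specified, and the absence of adjustment is declared openly. Declining to adjust in a pilot dose exploration is a defensible choice. It would stand if the SAP gave it as the reason, but it does not. The SAP states a formal null hypothesis, an alpha and a power claim for these comparisons, and it keeps a separate exploratory tier. The random effects model does not resolve the matter, because it is added to quantify the change and no joint test from it is named as deciding the hypothesis.

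A second point stands in part: the primary objective asks about an increase, so the 13%, which also counts false decreases, is not the rate of false claims of benefit. That rate is about 6.4%. It is still more than twice the single-test 2.5%.

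On power, a reader might infer that the trial is underpowered or that 80% is an arithmetic error. The SAP does not support that. Taking 2.14 as the SD of the difference gives more than 80%, and a correlation of about 0.35 gives exactly 80%. The protocol, not shown here, may hold the full derivation. What remains is that section 1.3.4 says the figures it quotes indicate 80%, and on their own they do not. Nor does it follow that a null result could not be interpreted. The completed trial will be read from its estimates and 95% intervals, not from its planned power. The mention of the controls is loose wording and would not mislead the analyst, since section 5.3.1 is explicit.

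**Conclusion.** Both parts hold in a limited form.

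The primary hypothesis, as worded and tested, carries about a 13% chance of false rejection instead of 5%. This assumes that no dose works and that any one significant dose counts as rejection. The range is about 9% to 14% over correlations of 0.9 down to 0 between the differences. For false increases alone it is about 6.4% against 2.5%.

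The 80% power is underivable from the inputs cited, but it is not shown to be wrong. On those inputs, power per dose at 19 evaluable lies between 62% and 98.5% for ρ from 0 to 0.7, so the true figure could be on either side of 80%. This part is a documentation fault that changes neither the sample size nor the analysis. The multiplicity part affects what the trial may claim and should be settled before database lock.

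**What to change.** **Section 4.2.** State that the three dose-versus-baseline paired t-tests are the tests of the primary hypothesis and are adjusted by Holm at family-wise alpha 0.05. State that the random effects model is for estimation and that exploratory comparisons are unadjusted. If the sponsor prefers no adjustment because this is a pilot, the section should say so. The three comparisons should then be reported as estimates with confidence intervals, with no claim that the primary hypothesis is rejected at 5%.

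**Section 1.3.4.** Restate power as a paired calculation: a 1.66 pmol/L difference, 19 evaluable T1D participants, a declared SD of the paired difference with a range, the sidedness and the per-dose alpha used. Take the controls out of the sentence on primary power.

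**Cost.** These are wording changes, and section 1 provides for amending the SAP and finalising it before database lock. Under Holm, per-dose power falls by about 5, 8 or 12 points (ρ = 0.5, 0.35, 0) if all doses work, and by about 13, 17 or 19 points if only one does. The unadjusted option costs no power but gives up the formal claim. Neither needs extra participants.

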### **4.3 Planned Subgroup Analyses**

No subgroup analyses have been planned.

### **4.4 Derived variables**

Body mass index (BMI) variable will be derived from height and weight of participants using the formula below:

- $BMI = \text{Weight (kg)} / (\text{Height (m)})^2$ .

## **5 Statistical Methodology**

The statistical methodology for the main primary analysis is described below. Analyses will use the ITT population (section 3.2) for primary and exploratory endpoint(s), and safety population for safety endpoint(s). All statistical significance will be assessed using

an alpha value of 0.05 (95% confidence interval). The summary statistics and statistical estimates will be presented with one decimal place unless more decimal places are needed to interpret the data. All p-values will be rounded to 3 decimal places. All Tables and Figures documented in this SAP are shell versions of the anticipated results and output formats of the analyses to be conducted for the study.

## 5.1 Disposition of Patients

Enrolment according to the population described in section 3.2 will be summarised and listed. The rate and relevant reasons for discontinuation will be described by treatment and period.

## 5.2 Baseline Characteristics

The demographic, clinical and anthropometric characteristics as well as the medical history data will be tabulated and summarised. We will use descriptive statistics [counts (percentage) for categorical variables and mean (standard deviation) or median (interquartile range) for continuous variables] to summarize baseline characteristics of participants, as well as outcome variables for each treatment period. When a variable is measured over time it will be summarised by period. The demographic data will include age, gender, body weight, height, SBP, DBP, resting heart rate, HbA1c, FBC, U&E, LFTs, Blood Glucose, Plasma glucagon, Plasma C-peptide and Plasma somatostatin by diabetes status (T1D/non-DM) **Table 5**.

## 5.3 Primary Endpoint Analysis

### 5.3.1 Primary Efficacy Analysis

To determine whether people randomised to glibenclamide at 0.3mg, 0.6mg or 3mg daily for 14-18 days can change the counter-regulatory plasma glucagon concentration measured in pmol/L at 40min during induced hypoglycaemia compared to baseline (pre-treatment) in T1D group only. We will use 3 separate paired t-tests to compare plasma glucagon concentration (pmol/L) at baseline and at each glibenclamide dose step i.e. 0mg vs 0.3mg, 0mg vs 0.6mg, and 0mg vs 3mg. We will also use linear random effects model [6] using plasma glucagon concentration (pmol/L) at each glibenclamide dose step as dependent variable and including treatment, period, and sequence of treatment to account for within-subject correlation to quantify the magnitude and direction of the change (increase/decrease). We will also adjust for age, gender, body weight, height, SBP, DBP and resting heart rate.

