## 1.2 Study Design

The LEGEND-D trial is a pilot, randomised cross-over, single-centre, non-blinded, clinical trial which aims to investigate the effect of 3 low doses of glibenclamide (0.3mg, 0.6mg and 3mg/day) assigned in all possible sequences followed by dapagliflozin (single dose of 10mg) on the plasma glucagon response during induced hypoglycaemia in people with type 1 diabetes, compared to non-diabetic individuals (**Figure 1**). The trial will be conducted by the Oxford Centre for Diabetes, Endocrinology and Metabolism (OCDEM) Clinical Research Unit (CRU) at the Churchill Hospital.

**Figure 1:** Trial flow chart

[figure not shown]

A summary timeline of the trial is shown on figure 1 above. For participants with T1D, the trial is divided into 5 steps, and involves 5 hyperinsulinaemic hypoglycaemic clamps. Once step 1 (no medication) has been completed, the participants with T1D will be randomised to a sequence of glibenclamide doses for the subsequent steps, followed by a single dose of 10mg dapagliflozin. There will be a washout phase of at least 48 hours between each step (the half-life of the glibenclamide suspension is 8 hours) [1]. Participants without diabetes will undergo a single hyperinsulinaemic hypoglycaemic clamp, as they will not receive any study medication.

The total daily dose as defined by the dosing schedule will be split into AM and PM as shown in

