## 2 Endpoints

### 2.1 Primary Endpoints

#### 2.1.1 Definition and Derivation of Primary Endpoint(s)

The primary endpoint in this study is the difference in plasma glucagon response during induced hypoglycaemia and baseline (pre-treatment). It is defined as the concentration of plasma glucagon measured in pmol/L at 40min during the hypoglycaemic phase of the hyper-insulinaemic hypoglycaemic clamp, at baseline and at each dose step i.e. 0.3mg, 0.6mg or 3mg of glibenclamide (T1D group only).

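### The random effects model in SAP 5.3.1 cannot, as written, estimate change from baseline, because the untreated clamp is always the first period

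*SAP*

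**What the plan says.** SAP 1.2 (Study Design) fixes the order of the clamps: "Once step 1 (no medication) has been completed, the participants with T1D will be randomised to a sequence of glibenclamide doses". The doses are "assigned in all possible sequences followed by dapagliflozin (single dose of 10mg"), so three doses give six sequences. The 0 mg clamp belongs to none of them and always comes first.

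SAP 2.1.1 defines the primary endpoint as glucagon at 40 minutes "at baseline and at each dose step i.e. 0.3mg, 0.6mg or 3mg of glibenclamide (T1D group only"), which makes four clamps per participant.

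SAP 5.3.1 gives two analyses.
- **Paired tests.** "We will use 3 separate paired t-tests to compare plasma glucagon concentration (pmol/L) at baseline and at each glibenclamide dose step". The three contrasts that these tests address are named there as "0mg vs 0.3mg, 0mg vs 0.6mg, and 0mg vs 3mg".
- **Model.** A random effects model is added. Its response is described by the words "using plasma glucagon concentration (pmol/L) at each glibenclamide dose step as dependent variable". Its fixed terms and its purpose are stated next, in the form "including treatment, period, and sequence of treatment to account for within-subject correlation to quantify the magnitude and direction of the change". The covariates follow in a separate sentence: "We will also adjust for age, gender, body weight, height, SBP, DBP and resting heart rate".

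The section does not say how period is coded or how the step 1 clamp enters the model. Baseline glucagon is not among the covariates. SAP 5.3.2 plans no sensitivity analysis for the primary endpoint.

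**The concern.** The model is given the task of estimating how much each dose changes glucagon relative to the untreated clamp. Treatment, period and sequence are the usual terms for a crossover in which every treatment appears in every period. That holds here for the three doses but not for 0 mg, which occurs only in the first period. Any difference between the first clamp and later ones (habituation to repeated hypoglycaemia, assay or calendar drift) cannot be separated from the difference between no drug and drug.

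At stake is the model-based effect estimate for the primary objective. Fitted with period as a factor, it would rest on an arbitrary coding choice. Fitted to the dose steps alone, it would not address the objective.

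**Working it through.** **Inputs.** 20 participants with type 1 diabetes and a mean glucagon of 5.54 pmol/L (SD 2.14), both from SAP 1.3.4. The clamp order is from SAP 1.2 and the model terms from SAP 5.3.1. The participants are spread over the six sequences as evenly as 20 allows. The SAP states no figure for the model that could be reproduced first.

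**1. All four clamps as responses, period as a factor.** Columns: intercept 1 + treatment 3 + period 3 + sequence 5 = 12. In every row the 0 mg indicator equals the period 1 indicator, so the three dose indicators sum to the same vector as the period 2 to 4 indicators. The rank is 11.
- A contrast is estimable only if it lies in the row space of the design matrix. None of 0.3 − 0, 0.6 − 0 and 3 − 0 mg does. All dose-versus-dose contrasts do.
- Replacing sequence by participant effects gives 26 columns, rank 25, and the same result.

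**2. What software would report.** One column must go. Take no drug effect and an assumed upward drift of 10% of the mean per successive clamp: 0.10 × 5.54 = 0.554 pmol/L. Each dose-minus-0 mg estimate then equals the drift accumulated by the reference period:

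| Period column dropped | Dose − 0 mg (pmol/L) |
|---|---|
| Period 2 | 1 × 0.554 = 0.554 |
| Period 3 | 2 × 0.554 = 1.108 |
| Period 4 | 3 × 0.554 = 1.662 |

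The fit is identical in all three cases. The planned 30% increase is 0.30 × 5.54 = 1.662. The match with the last row follows from choosing three steps of 10%. It shows the scale and is not evidence that such a drift exists.

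**3. Only dose-step clamps as responses (the literal text).** Columns: 1 + 2 + 2 + 5 = 10, rank 10. The model is sound, but it has no 0 mg level and no baseline glucagon covariate, so it says nothing about change from baseline.

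**4. All four clamps, period as a straight line.** Participant-effects model: 24 columns, rank 24. The contrasts are estimable, but only by extending a line fitted over the randomised steps back to clamp 1. In units of the within-person residual SD, the standard error of dose − 0 mg is 0.437 to 0.454, against 0.316 with no period term. The SAP does not specify a linear period.

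**5. The paired t-tests under the same drift.** With the doses balanced over steps 2 to 4, the average shift is (0.554 + 1.108 + 1.662) / 3 = 1.108 pmol/L. The SAP gives no within-person correlation ρ, so the SD of the difference is taken as 2.14 × √(2(1 − ρ)). Two-sided rejection at 0.05 with n = 19 (20 less 5% dropout) and no drug effect:

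| ρ (assumed) | SD of difference | 10% drift | 5% drift |
|---|---|---|---|
| 0 | 3.03 | 33% | 12% |
| 0.35 | 2.44 | 47% | 16% |
| 0.5 | 2.14 | 57% | 19% |
| 0.7 | 1.66 | 79% | 28% |

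**6. Period coded only among the three randomised steps** (sum-to-zero, set to 0 at baseline). Columns: 1 + 3 + 2 = 6, rank 6; with sequence kept, 11 columns, rank 11. All three dose − 0 mg contrasts are estimable. Under the drift in step 2 each equals 1.108, the same average shift as in step 5. The standard error factor is 0.316 to 0.317.

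**The case against.** The paired t-tests come first in SAP 5.3.1, target exactly the three required contrasts, and give a signed mean difference with a confidence interval. The aliasing does not touch them. The wording on period also leaves room for codings that are of full rank. A random participant effect is implied by the model's name and by its stated concern with within-subject correlation, so its absence from the text is a matter of detail. The recoded model returns nearly the numbers that the paired tests already give: with balanced sequences (n = 18) the estimates and the standard error factor (0.333) are the same. This is a pilot, and SAP 1.2 openly places step 1 before randomisation.

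All of that stands, and it limits the weight of the point. It does not rescue the model sentence: the usual factor coding and the literal dose-step reading both fail at the stated task, and the linear escape is unstated and rests on extrapolation.

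A reader might infer that the trial cannot estimate or test dose versus baseline at all, or that its randomised information goes unused. The SAP does not support either inference. The paired tests deliver the first, subject to order confounding. The model does estimate dose-versus-dose contrasts, and it is part of the primary analysis.

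**Conclusion.** The model sentence is wrong as written and should be fixed. The rank result needs only the clamp order in SAP 1.2 and a factor coding of period. The failure of the dose-step reading needs only the text of SAP 5.3.1. Neither depends on an assumed figure.

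The sizes do. The values 0.55, 1.11 and 1.66 pmol/L rest on an assumed linear drift, and the rejection rates of 33% to 79% on that drift and on a correlation between 0 and 0.7. The documents give no evidence of such a drift or of its direction.

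The confounding of dose versus baseline with clamp order is a feature of the design. It affects the paired tests as well, and no recoding removes it. SAP 5.3.1 does not acknowledge it.

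**What to change.** In SAP 5.3.1, replace the model sentence with one stating that the model:
- uses all four clamps (0, 0.3, 0.6 and 3 mg) in the type 1 diabetes group;
- has a random participant intercept and treatment at four levels;
- codes period only among the three randomised steps, sum-to-zero and 0 at baseline.

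This gives dose versus baseline averaged over the randomised periods. Then add two statements. First, dose versus baseline is not a randomised comparison and is confounded with clamp order, in this model and in the paired t-tests. Second, the period-adjusted contrasts among 0.3, 0.6 and 3 mg are reported as the randomised supporting evidence.

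Dropping the covariates, using Kenward-Roger degrees of freedom, or adding a trend in log dose are optional preferences. The cost is SAP wording and one respecified model, with no new data. The downside is that the SAP must openly qualify its main contrast.
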